
**Aim 1.** To assess the overall impact, both intended and unintended, of the Choosing Wisely Initiative.

H1.1. Patients treated in facilities that focus on hypoglycemia risk reduction will have a lower likelihood of overtreatment compared to those treated in other facilities.

H1.2. Patients treated in facilities that focus on hypoglycemia risk reduction will have the same likelihood of undertreatment compared to those treated in other facilities.

**Aim 2.** To assess the impact of commitment to quality, teaching intensity, and safety culture on patients' likelihood of overtreatment.

H 2.1a. Patients treated in facilities with higher levels of commitment to quality are less likely to be overtreated compared to those in facilities with lower levels of facility commitment to quality.

H2.1b. Patients treated in facilities with higher level of teaching intensity are less likely to be overtreated compared to those in facilities with lower level of teaching intensity.

H2.1c. Patients treated in facilities with higher level of safety culture are less likely to be overtreated compared to those in facilities with lower level of teaching intensity.

**Aim 3.** To identify configurations of the implementation strategy (Choosing Wisely toolkit), provider characteristics and organizational level factors that are associated with successful reduction of overtreatment rates by comparing high and low performers. Our sample size will be insufficient for formal hypothesis testing, but we will examine the following research questions using matrix and qualitative comparative analyses:

RQ3.1. Which configurations of the Choosing Wisely toolkit are associated with greater reduction in overtreatment rates?

RQ3.2. Which configurations of provider characteristics and organizational factors are associated with greater reduction in overtreatment rates?

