differences in probability of overtreatment (e.g., A1c <6.5%) rates for facility-level predictors in a two-level model. We note that in 2009, there were ~205,000 with insulin/sulfonylurea who were  $\geq 75$  years old, or with either diagnosis of dementia or cognitive impairment, or having serum creatinine >2.0 mg/dl from at least 130 VA medical centers across the nation. We also estimated that the number of such high risk patients in each facility range from 300 to 7,000. Based on 2009 data on the high risk patients, 28.6% (facility variation: 24.7%-32.7%) had their last A1c values < 6.5%. Since 2009, the number of patients has increased. We assumed a

[figure not shown]

“control/reference” group probability of overtreatment of 0.290 based on our data from 2009. We assumed a Type I error rate of 0.05 for two-sided tests. We conducted power analysis based on 130 facilities and 300 (or 150) patients per facility. Figure 3 shows the relationship between power achieved and the overtreatment probability for the treatment group ( $P(TX)$ ). The graph shows that when  $P(TX)$  moves away from 0.29 (namely, the group contrast becomes larger) and  $n$  is bigger, power increases. For example, we will have more than 0.8 power if  $P(TX) \leq 0.273$  (detectable minimum group difference ( $d$ ) = 0.017) for  $n=300$  and  $P(TX) \leq 0.268$  for  $n=150$  ( $d=0.022$ ). Our power calculations are based on 130 facilities with either 300 or 150 patients each and thus are extremely conservative and indicate that there will be sufficient power for subgroup analyses. The power calculation also has to consider the dependence among observations nested within the same cluster. However, we note that intraclass correlation for binary outcomes is less

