straightforward than for continuous outcomes. In fact, Spybrook and Raudenbush who developed the Optimal Design software stated: “In the case of a binary outcome, we do not typically standardize the model because the level-1 variance is heteroskedastic, which makes the meaning of the intraclass correlation,  $\rho$ , uninformative.” Our conservative approach will accommodate even large intraclass correlations. Aim 3’s selection of high and low performers is based on changes in facility-level overtreatment rates. We cannot be certain which facilities will choose to focus on hypoglycemia risk reduction as opposed to another Choosing Wisely topic area or none at all. Previous experience (courtesy of National Program Director for Medicine) suggests that a minimum of 4-6 VISNs will choose the hypoglycemia risk reduction focus, each with an average of 5 facilities. In addition, sites in other VISNs may implement this intervention. We obtained data from 2009 and 2010 to assess year to year variation. This allowed us to estimate power based on a paired  $t$  test for a simple pre-test post-test design. One hundred random samples of 20 facilities were chosen. The mean  $\pm 1$ SD change in overtreatment rate for the A1c <6% threshold, a level that puts patients at the highest risk was an absolute percent reduction of  $-0.9 \pm 2.4$ , e.g., an overtreatment rate falling from 10% to 9.1%. Based on paired  $t$  test, our study will require as few as 15 facilities to detect an absolute overtreatment rate reduction of 2.9, e.g., 10% to 7.1%, with 85% power, even assuming as little as 50% correlation between the SDs of each of the two measurements. This compares favorably with preliminary work from VISN 12 which showed that rates of overtreatment fell by 4.6 to 5.9 at the three A1c thresholds.

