**Comorbidities.** Using ICD 9CM codes we will create indicators of advanced complications of diabetes, limited life expectancy, cardiovascular or ischemic vascular disease, and major medical and mental health conditions that would impact benefit or risk of tight control based upon previously published taxonomies.

**Demographic Variables.** We have developed algorithms to process multiple entries of patient data over time and from a variety of sources to optimize the demographic information available for research. Sources include many years of VA inpatient and outpatient data with multiple fields and Medicare data. Consequently, we have nearly complete and largely confirmed assignments for most variables, including age and sex. Because of limitations in data concerning race/ethnicity, we will not assess this variable.

**2.4.6. Identification of High and Low Performers.** High and low performers will be identified based on changes in facility overtreatment rates pre- and post-initiative (rather than on absolute values). Those with the greatest (high performers) and least reduction (low performers) in overtreatment rates will be selected. To

minimize issues related to regression to the mean, we will focus on facilities that were mid-performing at baseline (2nd and 3rd quartiles). See Fig. 4. Among the middle-performing facilities at baseline, we will select those facilities with the greatest reduction in overtreatment rates (high performers) and those with the least reduction (low performers). We will also select from among the highest performers at baseline who improved at all as well as some low performers at baseline who stayed low. It is impossible to know how many facilities will fall into these categories; but we are anticipating approximately 5-10 in each group (total n~30). Aim 3 does not include hypothesis testing, but is instead looking for identifying patterns of provider and facility characteristics associated with performance status (high vs. low). Our methods of analyses (matrix and qualitative comparative analysis) allow for a small sample size. Performance status will be determined independently of Choosing Wisely participation status; selected sites will likely include those facilities choosing the hypoglycemia initiative alone or both hypoglycemia and low back pain initiatives. If entire VISNs participate

[figure not shown]

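### The Aim 3 power figure holds only after an unstated subtraction of the 0.9-point background fall, and the facility-level pre-post comparison and raw-change ranking need tightening

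*Protocol*

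**What the plan says.** Section 2.4.4 turns to Aim 3 after the hierarchical power calculation. It takes facility data from 2009 and 2010, before any initiative, and says of them: "This allowed us to estimate power based on a paired" t test "for a simple pre-test post-test design". The change over that year at the A1c <6% threshold is given as a fall of 0.9 points with an SD of 2.4. The claim follows: the study will "require as few as 15 facilities to detect an absolute overtreatment rate reduction of 2.9, e.g., 10% to 7.1%, with 85% power", with a correlation of 50% between the two measurements. No significance level is given for this test. The one given earlier in the section is "We assumed a Type I error rate of 0.05 for two-sided tests".

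Section 2.4.5.1 sets the overtreatment threshold at 6.5% and keeps 6.0% and 7.0% for sensitivity analysis.

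Section 2.4.6 chooses the Aim 3 sites from the change in facility rates, mainly within the two middle baseline quartiles: "Those with the greatest (high performers) and least reduction (low performers) in overtreatment rates will be selected". Section 2.4.4 puts facility size on record: "the number of such high risk patients in each facility range from 300 to 7,000".

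The Specific Aims say of Aim 3: "Our sample size will be insufficient for formal hypothesis testing". Section 2.5 nonetheless relies on a paired pre-post analysis within each facility to ease the concern that adopters and non-adopters differ at baseline.

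**The concern.** Taken as worded, the power sentence describes a test of a 2.9-point fall against no change, and for that test 15 facilities and 85% power do not go together. An analyst who follows the wording would test raw change against zero and would count a fall that was already under way as an effect of the initiative.

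The same weakness touches section 2.5. Pairing a facility with itself removes stable differences between facilities, but not a trend over time.

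The ranking raises a separate question. The change in a facility with 300 patients carries far more sampling error than the change in one with 7,000, so the extremes of a raw ranking tend to be small facilities. About 900 surveys, 150 interviews, the qualitative comparative analysis and 8 site visits rest on the resulting labels of high and low performer.

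**Working it through.** **Inputs.** From section 2.4.4: background change −0.9, SD 2.4 (A1c <6%); target fall 2.9; 15 facilities; power 85%; correlation 0.5. Two-sided 0.05 is carried over from the hierarchical calculation (an assumption). If 2.4 is the SD at each time point, the SD of change is 2.4 × √(2 × (1 − 0.5)) = 2.4, so both readings give the same value.

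**Formula.** Power = P(|T| > t₀.₉₇₅,ₙ₋₁), where T is noncentral t with n − 1 degrees of freedom and noncentrality δ√n / 2.4.

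**Reproducing the plan's figure.**

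| Effect δ | n | Noncentrality | Power |
|---|---|---|---|
| 2.9 − 0.9 = 2.0 | 15 | 3.23 | 0.851 |
| 2.9 | 15 | 4.68 | 0.991 |
| 2.9 | 8 | 3.42 | 0.833 |
| 2.9 | 9 | 3.63 | 0.886 |

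The net effect of 2.0 reproduces 15 facilities and 85%; the smallest effect detectable with 85% power at 15 facilities is 1.998. The gross effect of 2.9 does not reproduce it. An effect of 2.9 with zero correlation (SD of change 2.4 × √2 = 3.39) gives 0.868 and also needs 15 facilities, but that contradicts the stated 50%.

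**Drift alone, tested against zero.** With δ = 0.9 and SD 2.4, the rejection probability is 0.27 at 15 facilities, 0.36 at 20 and 0.51 at 30. The 20 and 30 are the protocol's own expected minimum: 4 to 6 VISNs with 5 facilities each.

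**Threshold.** Section 2.4.4 gives a rate of 28.6% at <6.5% and uses 10% as its example at <6%. The binomial variance per patient is 0.286 × 0.714 = 0.204 against 0.10 × 0.90 = 0.090, so the sampling part of the SD is about √(0.204 / 0.090) = 1.5 times as large at <6.5%. The protocol gives no SD of change at that threshold.

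**Ranking.** With independent patient samples in the two years, the sampling SD of change at <6.5% is 100 × √(2 × 0.204 / n): 3.7 points at n = 300 and 0.8 at n = 7,000. Ranking was simulated for 65 mid-baseline facilities (half of 130), log-uniform sizes from 300 to 7,000, 8 selected at each end:

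| Assumed scenario | Correct true tertile, raw | Correct true tertile, shrunken |
|---|---|---|
| <6.5%, true SD 1.5, independent samples | 72% | 82% |
| <6.5%, sampling variance halved for patient overlap | 81% | 89% |
| <6% (rate 10%), true SD 2.0 | 90% | 95% |

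Across the scenarios tried, the ranges were about 72–92% raw and 82–96% shrunken. The smallest third of facilities supplied about 42–52% of the selected sites under raw ranking, against 33% if size played no part.

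**The case against.** The strongest reply is that the number is right. The 0.9 stands one sentence before the claim, subtracting it returns 85% at 15 facilities, and this suggests that the calculation removed the background fall. That stands. A reader might infer that the figure cannot be derived from its inputs, or that the power calculation credits the background fall to the initiative; the documents support neither.

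A reader might also infer that the −0.9 mean distorts the choice of high and low performers. It cannot: a shift common to all facilities leaves the ranks unchanged, and section 2.4.6 sets performance status without regard to participation. Only the spread and the unequal precision matter.

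Next, the declared test of effect is Aim 1, which compares four concurrent groups of facilities with adjustment for earlier glycemic status, while Aim 3 tests no hypothesis. That also stands, and it limits the damage. It does not cover section 2.5, where the paired analysis is offered as a remedy for non-random adoption without any word on trend.

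Last, the selection already has safeguards: middle quartiles, a statistical method for positive deviants within a VISN, and a check at two years. The simulation rests on assumed sizes and true SDs, and few sites are badly misplaced: about 7% fall in the opposite tertile in the least favorable scenario. This is fair. The safeguards do not address unequal precision in the main ranking, however, and shrinkage improved placement in every scenario.

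**Conclusion.** The point holds in a limited form. The figure of 15 facilities and 85% power is correct for a fall of 2.0 points beyond a 0.9-point background fall at A1c <6%. As worded, a paired test of 2.9 points, it describes a test with power 0.99 at 15 facilities. If facility change were tested against zero, drift alone would give a positive result in 27% to 51% of studies of 15 to 30 facilities. The threshold behind the SD is not that of the main outcome.

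This rests on two-sided 0.05 and on 2.4 being the SD of change across facilities. If 2.4 were instead the SD of means over the samples of 20, the facility SD would be 2.4 × √20 = 10.7 and power at 15 facilities only 0.10 to 0.16; the close match at 2.4 speaks against that reading. Even the net version treats one earlier year's drift as a known constant.

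Raw ranking is not an error in an exploratory aim, but it over-selects small facilities and is cheap to improve. Its percentages are illustrative.

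**What to change.** 1. In section 2.4.4, say that the detectable effect is 2.0 points beyond a 0.9-point background fall, at the <6% threshold, and name the null value and significance level. Then recompute for <6.5% from the sponsor's own 2009 and 2010 data. Do not carry over the SD of 2.4. In particular, a two-sample comparison of 15 facilities with the other 115 gives power 0.85 for 2.0 points at that SD, but only 0.67 at SD 3.0 and 0.54 at SD 3.5, before any allowance for VISN clustering, so 0.85 should not be quoted for <6.5%.
2. In sections 2.4.4 and 2.5, judge any facility-level pre-post change against the change in concurrent non-participating facilities, not against zero.
3. In section 2.4.6, rank facilities on shrunken (empirical-Bayes) change. The facility random effects planned in section 2.4.8 provide the framework.
4. Set the baseline quartiles from an earlier year, if the 2012 to 2016 data requested in section 2.4.7 cover it in full, so that one year does not both define the quartile and enter the change.

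The cost is rewording, one recalculation and a re-ranking with data already requested. The downside is that fewer very small facilities would be selected.

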## 2.4.5. Dependent and Independent Variables (Quantitative)

### 2.4.5.1. Dependent Variables (Outcome Measures for Summative Evaluation)

**Overtreatment and undertreatment.** Using the last A1c value in a time period we will define overtreatment if it is less than the thresholds of 6.5% (we will evaluate 6.0% and 7.0% for sensitivity analysis). If the same A1c value is greater than 9.0%, it is considered undertreatment. Those in the range of 6.5% to 9.0% are considered to be in moderate glycemic control and will be used as the reference group in statistical analyses.

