**2. Specific Aims.** Implementation of practice change is difficult and large scale implementation is particularly difficult. Among the challenges facing the healthcare system in general and healthcare organizations such as VHA is the overuse of low value care. Reducing low value care has become a recent focus of VA's quality improvement efforts as evidenced by the VA's creation of a Choosing Wisely Taskforce to recommend how this national initiative can be implemented. Improving medication safety also constitutes an attempt to reduce low value or potentially harmful care. Critical issues of overuse of low value practices and medication safety intersect in overtreatment of diabetes (DM). Specifically, (over)intensive glycemic control increases hypoglycemia risk and morbidity without providing meaningful benefit. Our work indicates that among patients with diabetes who are at high risk for hypoglycemia – due to use of specific hypoglycemic agents, age, and/or significant comorbidities – up to 50% are potentially overtreated, as defined by an A1c <7%. National recognition for hypoglycemic safety is evidenced by the creation of a Health and Human Services Federal Interagency Workgroup (with representatives from VA and DoD) to address adverse drug events, including those from hypoglycemic agents. Moreover, the Choosing Wisely Initiative to reduce low value care led by the American Board of Internal Medicine Foundation includes an American Geriatric Society recommendation to “not treat most persons over 65 years of age with medications to reduce the A1c<7.5%.” For most physicians this involves changes to their current clinical practice. VHA's soon to be announced response to the Choosing Wisely Initiative will include hypoglycemic safety as one of its targeted conditions (see letters of support from [name]). Our goal is to study the implementation of the Choosing Wisely Initiative as it plays out at the facility and practitioner levels. We will assess the concomitant implementation of processes of reducing clinically inappropriately tight glycemic control (de-implementation) as well as assess the effectiveness of a toolkit being promoted by this initiative. Because focus on this initiative could have the unintended consequence of paying less attention to poor glycemic control (A1c>9%), we will also assess undertreatment. In so doing, we will inform both VHA and the broader federal health community. We propose three specific aims and associated hypotheses (H) and research questions (RQ):

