**Aim 1.** To assess the *overall* impact, both intended and unintended, of the Choosing Wisely Initiative. All analyses will be conducted for various subgroups of high risk patients. Due to the nature of the outcome variable in the quantitative aims (Aims 1 and 2), the primary statistical technique for these two aims will be logistic regression. The “logit” (i.e., log of odds) of the presence of an event is regressed on a list of independent variables. We will use odds ratios (=exponentiation of the estimated regression coefficients) and their confidence intervals for the hypothesis testing. An odds ratio larger (smaller) than 1 with a 95% confidence interval not containing 1 indicates a higher (lower) likelihood of the occurrence of an event for the group in comparison relative to the reference group in an independent variable. In Aim 1 we will use multinomial logistic regressions to model the outcome variable, a polytomous variable. In the models the polytomous variable is treated as a nominal variable and a value in the variable is treated as the reference group; separate logistic regression models for the probabilities of non-reference groups against the reference group are constructed and estimated simultaneously. This approach is more efficient than separately conducting two logistic regression models (i.e., the overtreated versus those in moderate control and the

undertreated versus those in moderate control). The primary exposure variable in both H1.1 and H1.2 is the group indicator variable. Along with the previously listed independent variables, a patient's glycemic control status in the pre-initiation period will also be included in the models as a control variable. We will assess both the implementation and sustainability phases of the initiative.

**Aim 2.** To assess the impact of facility commitment to quality, teaching intensity, and safety culture on patients' likelihood of overtreatment. We will use a similar modeling strategy to Aim1 for this aim but employ binary logistic regression models, because the hypotheses focus on overtreatment (a binary variable: overtreatment versus moderate control). We will construct separate models for each of H2.1a, H2.1b, and H2.1c. We will also evaluate the associations among the three primary exposures variables in the hypotheses, and construct a statistical model including all three variables and compare with the separate models.

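### H1.2 tests undertreatment against moderate control, a category that the intended benefit enlarges, so its odds ratio is biased modestly below 1

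*Protocol*

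**What the plan says.** Section 2 gives the reason for measuring undertreatment: "this initiative could have the unintended consequence of paying less attention to poor glycemic control (A1c>9%), we will also assess undertreatment". H1.2 then states that patients in facilities focusing on hypoglycemia risk reduction "will have the same likelihood of undertreatment compared to those treated in other facilities".

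Section 2.4.5.1 defines the outcome: "If the same A1c value is greater than 9.0%, it is considered undertreatment". Patients between 6.5% and 9.0% "are considered to be in moderate glycemic control and will be used as the reference group in statistical analyses".

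Section 2.4.8 sets the test: "In Aim 1 we will use multinomial logistic regressions to model the outcome variable, a polytomous variable". The second of its two contrasts is the "undertreated versus those in moderate control". Hypotheses are tested by odds ratios "and their confidence intervals for the hypothesis testing". An odds ratio above (below) 1 "with a 95% confidence interval not containing 1 indicates a higher (lower) likelihood of the occurrence of an event". Pre-initiation glycemic status enters as a control variable.

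Two other places bear on the point. Section 2.4 names a hierarchical ordinal logistic model for Aim 1, not a multinomial one. Section 2.4.8 also opens all analyses with crude chi-square comparisons of proportions across levels of the independent variables.

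**The concern.** H1.2 is about a probability among patients: how many end up with A1c above 9%. The multinomial odds ratio is a ratio of two category shares, undertreated over moderate, and leaves the overtreated out. Its direction need not follow the direction of the probability of undertreatment, although section 2.4.8 reads it that way.

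The mismatch has a predictable sign. The initiative aims to move patients out of A1c below 6.5%, and most of those who move will land in 6.5–9.0%, the denominator of the harm odds. The more the initiative succeeds, the further the harm odds ratio is pulled down. The modelled measure of the unintended consequence named in section 2 is thus tied to the benefit, and it leans towards reassurance in the facilities where reassurance matters most.

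**Working it through.** **Inputs from the protocol.** Reference overtreatment probability 0.290; detectable values 0.273 (n = 300 per facility) and 0.268 (n = 150); 130 facilities; two-sided 0.05; facility range 24.7–32.7% (all section 2.4.4). VISN 12 falls of 4.6 to 5.9 points (section 2.4.4). At least 4–6 VISNs with an average of 5 facilities each choosing the hypoglycemia focus (sections 2.4.2 and 2.4.4).

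**Assumed.** The protocol gives no undertreatment rate, so u0 = 5%, 10% and 15% are used. The VISN 12 falls are applied at the 6.5% threshold and treated as between-group differences.

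**1. The plan's own figure.** No power is stated for undertreatment. For overtreatment, take a logit-scale two-level calculation with an assumed 65:65 split. The between-facility variance is [(logit 0.327 − logit 0.247)/(2 × 1.96)]² = 0.010. The variance of the difference is the sum over arms of (0.010 + 1/(n p(1−p)))/65. Power is 0.837 for 0.290 versus 0.273 (n = 300) and 0.851 for 0.290 versus 0.268 (n = 150). The stated figure of more than 0.8 is reproduced.

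**2. Odds ratio when undertreatment has not changed.** Let o, m and u be the overtreated, moderate and undertreated shares, with o + m + u = 1. Then OR = (u1/m1)/(u0/m0). If u1 = u0, OR = m0/m1, with m0 = 1 − 0.29 − u0 and m1 = 1 − o1 − u0. At u0 = 10% and o1 = 0.244, this is 0.610/0.656 = 0.930.

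| Fall in overtreatment | u0 = 5% | u0 = 10% | u0 = 15% |
|---|---|---|---|
| 1.7 points | 0.975 | 0.973 | 0.971 |
| 2.2 points | 0.968 | 0.965 | 0.962 |
| 4.6 points | 0.935 | 0.930 | 0.924 |
| 5.9 points | 0.918 | 0.912 | 0.905 |

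The correct value for H1.2 is 1 in every cell.

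**3. Largest rise that still gives OR at or below 1.** Setting OR = 1 gives u1/u0 = (1 − o1)/(1 − o0), which does not depend on u0: 0.727/0.710 = 1.024, 0.732/0.710 = 1.031, 0.756/0.710 = 1.065 and 0.769/0.710 = 1.083. At u0 = 10%, undertreatment could reach 10.24%, 10.31%, 10.65% or 10.83% and still read as no increase.

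**4. Sign and attenuation (u0 = 10%, fall of 4.6 points).**
- True rise to 10.5%: OR versus moderate = (0.105/0.651)/(0.10/0.61) = 0.984; OR versus all others = (0.105/0.895)/(0.10/0.90) = 1.056. The signs differ.
- True rise to 11.0%: OR versus moderate = (0.110/0.646)/(0.10/0.61) = 1.04; versus all others, 1.11. With a 5.9-point fall the pair is 1.02 and 1.11.
- Chance of a significant OR above 1 for that rise to 11.0% (normal approximation; assumed 25 focus and 105 other facilities, 300 patients each, between-facility variance 0.01): about 12% versus moderate against 62% versus all others with the 4.6-point fall, and about 6% against 62% with the 5.9-point fall.

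**5. Baseline adjustment.** Within a stratum of pre-initiation status, unchanged u and lower o again give OR = m0/m1 below 1; where o is unchanged, OR = 1. A pooled estimate therefore stays below 1. It lies closer to 1 than the unadjusted value, because patients who reach A1c above 9% mostly start moderate or undertreated, where overtreatment, and so the inflow to the reference category, is smaller. Fits to assumed transition tables (the protocol gives none; follow-up about 29% overtreated and 9% undertreated) gave about 0.93–0.96 at the VISN 12 falls.

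**The case against.** **Another model is named.** The ordinal model in section 2.4 has no moderate-control reference, and its upper split is A1c above 9% versus everyone else. It conflicts with section 2.4.8, however, and is no cure. Under proportional odds one coefficient governs both splits. A fall from 0.290 to 0.273 means a common odds ratio of (0.290/0.710)/(0.273/0.727) = 1.088 towards higher A1c. Undertreatment of 10% would then be fitted as 0.1111 × 1.088/(1 + 0.1111 × 1.088) = 10.8%, whatever really happened. That is a bias in the opposite direction.

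**Crude proportions are planned.** A reader might infer that a rise in A1c above 9% would be invisible. Section 2.4.8 does not support that, since bivariate comparisons by group come first. But those are unadjusted and are not the H1.2 test.

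**The larger figures lean on VISN 12.** This stands. Those falls are pre-post changes in one VISN across three thresholds, not between-group differences at 6.5%, and any secular fall shared by both groups cancels. The detectable differences give the smaller bias. A reader might also scale the masked rise to the roughly 205,000 high-risk patients. The documents do not support a headcount: it would need every patient exposed, with no comparison group left, and an undertreatment rate that the protocol does not give.

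**The masking is bounded.** This also stands. Only rises below the limits in step 3 are turned into an odds ratio at or below 1.

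**It is reporting detail.** A statistical analysis plan, not seen here, could add predicted probabilities. But the protocol itself fixes the odds ratio as the test and states how to read it, and that reading does not match H1.2.

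**Conclusion.** The point holds in bounded form. The stated test of H1.2 does not measure what H1.2 asserts, and it errs towards no harm whenever overtreatment is lower in the focus facilities. With undertreatment unchanged, the unadjusted odds ratio is 0.962–0.975 at the protocol's detectable differences. It is 0.905–0.935 if the between-group difference reached the VISN 12 falls, shrinking to about 0.93–0.96 after baseline adjustment on assumed transition tables. Unadjusted, relative rises in A1c above 9% of up to 2.4–3.1% or 6.5–8.3% respectively are read as no increase. Larger rises still give an odds ratio above 1, but attenuated and less often significant.

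The direction and the break-even ratios do not depend on the undertreatment rate. The odds ratios assume a rate of 5–15% and a reference overtreatment probability of 0.29, and the detection figures also rest on the facility split and between-facility variance given above. The point should be corrected, but the documents do not support calling the safety assessment blind to harm.

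**What to change.** In section 2.4.8, keep the multinomial model and add a sentence that H1.2 is judged on the model-standardised probability of A1c above 9% among all patients analysed in each participation group, with the between-group difference and its 95% CI. Report the odds ratio versus moderate control as supporting only. A binary model of A1c above 9% versus 9% or lower is an alternative with the same target, though not a numerically identical result. Amend section 2.4 so that it and section 2.4.8 name the same Aim 1 model.

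The cost is a short text change in two sections. The probabilities come from the same fitted model, and no new data are needed.
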